# Baby Steps – a structured group education programme with accompanying mobile web application designed to promote physical activity in women with a history of gestational diabetes: study protocol for a randomised controlled trial

**DOI:** 10.1186/s13063-018-3067-8

**Published:** 2018-12-12

**Keywords:** Randomised controlled trial, Gestational diabetes, Self-management, Patient education, Diabetes prevention

## Abstract

**Background:**

A diagnosis of gestational diabetes (GDM) is associated with an over sevenfold increase in the risk of developing type 2 diabetes (T2D), while among parous women with T2D, up to 30% have a history of GDM. Lifestyle interventions have been shown to reduce the risk of incident T2D in adults with impaired glucose tolerance, including in women with a history of GDM. The aim of this study is to establish whether a group self-management education programme, supported by a mobile web application, can improve levels of physical activity at 12 months in women who have had GDM.

**Methods:**

The study is a randomised controlled trial with follow-up at 6 and 12 months. Primary outcome is change in objectively measured average daily physical activity at 12 months. Secondary outcomes include lipid profile, blood pressure, glycated haemoglobin, obesity, smoking and alcohol status, self-reported physical activity, anxiety, depression and quality of life. Participants are recruited from maternity and diabetes departments in hospital trusts in two sites in the UK. Women aged > 18 years, with a diagnosis of GDM during any pregnancy in the previous 60 months are eligible. Participants need to have a good understanding of written and verbal English, be able to give informed consent and have access to a smart-phone. Women who are pregnant or have type 1 or type 2 diabetes are not eligible. In total, 290 participants will be recruited and randomly assigned, with stratification for age and ethnicity, to either the control group, receiving usual care, or the intervention group who are invited to participate in the Baby Steps programme. This comprises a group education programme and access to a mobile web application which provides an education component and interacts with a wrist-worn activity monitor providing automated messages, setting challenges and encouraging motivation.

**Discussion:**

If effective, the Baby Steps programme could be translated into a primary care-based intervention that women with GDM are referred to in the postnatal period. This could help them make lifestyle changes that could reduce their future risk of T2D.

**Trial registration:**

ISRCTN, ISRCTN17299860. Registered on 5 April 2017.

**Electronic supplementary material:**

The online version of this article (10.1186/s13063-018-3067-8) contains supplementary material, which is available to authorized users.

## Background

### Maternal outcomes following gestational diabetes

Around 700,000 women give birth in England and Wales each year; up to 5% of them have a diagnosis of diabetes in pregnancy [1]. Among women with diabetes in pregnancy, gestational diabetes mellitus (GDM; described as abnormal glucose tolerance which first develops or is recognised during pregnancy) constitutes around 85% of cases, with the remainder due to pre-existing type 1 diabetes (T1D) or type 2 diabetes (T2D). The aetiology of GDM is not completely known but is due in part to the inability of the maternal pancreas to secrete sufficient insulin to cope with pregnancy-induced insulin resistance in susceptible women. The incidence of GDM is on the rise, in part due to higher rates of obesity in the general population, including in women of childbearing age [2–4]. Estimates suggest that lifestyle factors such as obesity, smoking, unhealthy diet and physical inactivity may explain around 50% of the incidence of GDM [5].

A diagnosis of GDM is associated with adverse outcomes for both the mother and her affected offspring. These women have higher risks of pre-eclampsia, Caesarean sections and an over sevenfold increase in the risk of developing T2D, with the highest incidence occurring within five years of the index pregnancy [6–9]. Among parous women who have a diagnosis of T2D, ≤ 30% have a previous history of GDM, which means that pregnancy and the postnatal period within the first five years present a ‘golden opportunity’ to intervene and alter the natural course of a disease [10, 11]. Additionally, women with a history of GDM have 2–3 times higher incidence of hypertension and ischaemic heart disease so any intervention provided in the postnatal period has the added potential of reducing cardiovascular disease risk [8].

Fetal macrosomia (defined as birthweight > 4–4.5 kg) and large for gestational age (LGA) (defined as birthweight > 2 SD greater than mean or > 90th centile after controlling for age and sex) are two of the most common and serious offspring outcomes of GDM in pregnancy. Babies born to GDM mothers are 4–7 times likely to be macrosomic [12, 13]. Other perinatal complications which are also associated with hyperglycaemia during pregnancy include shoulder dystocia and birth injuries, neonatal hypoglycaemia and respiratory distress syndrome [14]. In the long term, offspring of women with GDM are at increased risk of obesity, hypertension, hyperlipidaemia and glucose intolerance starting from childhood and early adolescence thereby perpetuating the cycle [15–17].

### Role of lifestyle interventions to reduce T2D

There is evidence from observational studies that an active lifestyle (including increase in physical activity time and reduction in sedentary time) is associated with weight loss, improved glucose tolerance and lower risk of progression to T2D in women with a history of GDM [18, 19]. The Diabetes Prevention Programme showed, with a randomised controlled trial (RCT) design, that intensive lifestyle interventions reduced the risk of incident T2D in adults with impaired glucose tolerance (IGT) by around 40–60% [20, 21] and, in a subgroup of women with a history of GDM, by 53% and 35% over three and ten years, respectively, compared to standard care [22, 23]. Other trials have shown decreases in rates of pre-diabetes, weight, waist circumference and lipid levels [24–26]. Interestingly, treatment with metformin has been shown to confer no additional benefit to lifestyle interventions, presumably due to adherence issues and less weight loss in the first year of treatment when compared to the latter [22].

However, there are several barriers to lifestyle interventions in postpartum women with recent GDM, including lack of time, balancing work and family demands, and lack of childcare [27, 28]. Recently, a web-based lifestyle intervention program in 75 women in Boston, USA was deemed to be feasible and associated with significant weight reduction (3.3 kg below the control group) and higher likelihood of being below pre-pregnancy weight at 12 months postpartum [29]. The program particularly recommended gradually increasing physical activity to 150 min per week, including resistance training and making healthier dietary choices.

While most of the abovementioned trials have suggested that a combination of exercise, healthy diet and weight loss or weight maintenance protects against diabetes in postpartum women, there is a lack of evidence about the independent effect of physical activity in reducing progression from GDM to T2D, particularly in high-risk populations such as minority ethnic groups. Indeed, in observational series, increase in moderate to vigorous physical activity, independent of body mass index (BMI), was associated with reduction in the risk of T2D in women after pregnancy [18]. Among non-pregnant adults, every 2000 step per day change from baseline to 12 months is associated with an additional 8% decrease in the cardiovascular event rate [30].

The ongoing and completed intervention programmes for women with a history of GDM have been conducted largely in women of white American, Australian or European background [19, 23, 31, 32] and black, Hispanic and mixed minority American [24, 33–35]. Therefore, there is a paucity of information about the feasibility and effectiveness of similar programmes for women in the UK, particularly in those of South Asian ethnicity. It is known that up to one in five South Asian adults globally have T2D and the diagnosis is 4–5 times more common in South Asian adults in the UK, compared to a white reference group [36, 37].

Our study will therefore be novel in developing and testing an intervention that meets the cultural and social needs of women in a catchment area in that has a large multi-ethnic population (estimated to constitute 25–60% of the women diagnosed with GDM in the two research sites).

## Methods/Design

### Aims and objectives

To assess the effectiveness of a group education programme and accompanying online web support (Baby Steps programme) in improving objectively measured physical activity at 12 months in participants with a history of GDM compared to usual care.To assess the effect of the programme on other risk factors including lipid profile, blood pressure, resting heart rate, glycated haemoglobin (HbA1c), obesity, smoking and alcohol status, self-reported physical activity, anxiety, depression, quality of life, fruit and vegetable intake compared to usual care.To assess the acceptability, uptake and feasibility of delivering the programme to women who are at high risk of developing T2D, including those from ethnic minority backgrounds.

### Study design and setting

The study is a two-group (1:1), parallel RCT of women who have had GDM during any pregnancy up to 60 months before the point of recruitment and are therefore at risk of developing T2D. Figure 1 describes the flow of participants through the study. The RCT is being conducted in two sites in the UK, namely University Hospitals of Leicester NHS Trust (serving the catchment area of Leicester City and the county of Leicestershire) and George Eliot Hospital NHS Trust (serving the catchment area of North Warwickshire). The protocol was written in accordance with the Standard Protocol Items: Recommendations for Interventional Trials (SPIRIT) guidelines (see Spirit Fig. 2 and the SPIRIT Checklist, which is available as Additional file 1). The study is sponsored by the University of Leicester and ethical approval was granted by the East Midlands – Derby Research Ethics Committee. The study was prospectively registered (ISRCTN 17299860).

**Fig. 1 Fig1:**
[figure not shown]
Consort flow diagram

**Fig. 2 Fig2:**
[figure not shown]
Schedule of enrolment, interventions and assessments as per SPIRIT 2013

### Recruitment and informed consent

Potential participants are identified from hospital databases (both maternity and diabetes departments) and are sent a recruitment pack containing an invitation letter, a brief information leaflet detailing the study and a reply slip. Reply slips are returned to the local study team. A member of the study team then contacts the respondent by telephone to screen them and arrange a baseline visit to confirm their eligibility, take their informed consent and collect the baseline data. Following the telephone call, they are sent a letter confirming the details of the appointment and a copy of the full Patient Information Leaflet (PIL). This is sent with sufficient time to enable them to have at least 24 h to read the PIL. A reminder invitation is sent to non-responders 4–6 weeks after the initial invitation. Potential participants who do not respond to the reminder invitation within four weeks may be called by a member of the direct care team. The purpose of the call is not to coerce the women to take part but to confirm they have received the invitation and to find out whether they understand the information they have been sent and whether they have any questions. There is also the opportunity for women to self-refer in response to posters in community venues and publicity in the local media.

### Eligibility criteria

The inclusion criteria are as follows:women aged ≥ 18 years, with a diagnosis of GDM during any pregnancy resulting in delivery in the last 60 months;willing and able to attend the clinic and education sessions;able to speak and read English sufficiently to give informed consent and follow the education programme.

The exclusion criteria are as follows:currently pregnant;diagnosis of T1D or T2D;cancer (not in remission);severe diagnosed mental illness (e.g. schizophrenia, bipolar);previous surgical or medical intervention to treat obesity;lack of access to Internet;participated in another clinical intervention study in the previous 12 weeks.

Women who consent to join the study and are identified as a result of the baseline blood tests as having undiagnosed T2D (HbA1c > 6.4%) are withdrawn from the study and referred back to their general practitioner.

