### Randomisation and blinding

Study identification numbers are assigned sequentially and participants are individually randomised (1:1) stratified by age (< 30 years; ≥ 30 years) and ethnicity (White European; other) using a variable block size after their baseline assessment. The randomisation schedule was developed by an independent statistician and allocation of randomisation is carried out by a researcher based in Leicester who is independent of the team. Randomisation determines which group the participant is allocated to (control or intervention). After randomisation, participants in both groups are sent a letter informing them of the outcome of the randomisation. In addition, intervention participants are contacted by telephone to discuss the dates available for them to attend the Baby Steps programme. They are then sent a letter confirming the venue and dates and times of the programme. Since the intervention is a group self-management programme, participants and the local research teams cannot be blinded to the randomisation. The staff analysing the accelerometer data to derive the primary outcome are blinded to allocation.

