### Statistical analysis

Descriptive characteristics at baseline will be summarised by treatment arm. Numbers (with percentages) for binary and categorical variables and means (and standard deviations) or medians (with lower and upper quartiles) as appropriate for continuous variables will be presented. Preliminary graphical and tabular presentations of the data will be inspected for the correct statistical modelling assumptions.

The primary analyses will use a complete case population. For the primary outcome (change from baseline in total physical activity), treatment arms will be compared using linear regression with a binary indicator for randomisation group as the explanatory variable, terms for the stratification factors as confounders, and adjustment for the change in accelerometer wear time and baseline total physical activity. Sensitivity analyses will include a per-protocol analysis (defined as attending at least one of the two group education sessions, i.e. those randomised to intervention but not attending either group session will be excluded) and an intention-to-treat analysis where missing data will be imputed using multiple imputations. Interaction effects will be fitted between intervention arm and age (< median vs ≥ median), and ethnicity (White European vs other). If the interaction term is statistically significant then stratified analyses will be performed for that factor using the same model as the primary analyses. Secondary outcomes will be analysed using similar methods as the main analysis, with an appropriate model selected dependent on the distribution of the outcome.

The results of all comparative analyses will be presented with 95% confidence intervals and statistical significance for main effects will be assessed at the 5% level. All *p* values shown will be two-sided. Statistical significance for interaction effects will be assessed at the 10% level.

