### Protocol version

The current protocol version is Version 5; 25 May 2018. Four substantial amendments have been approved. Amendment 1 (before recruitment started) involved a change in the randomisation procedure (from an online software system to manual allocation using a randomisation schedule). Amendment 2 involved making telephone calls to non-responders. Amendment 3 involved a change in eligibility criteria (from recruited within 36 months of most recent delivery to recruited within 60 months of any delivery). Amendment 4 involved carrying out qualitative interviews with participants from the intervention arm.

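### Entry runs from soon after birth to 60 months after a GDM delivery, but the fixed model and interactions leave out time since delivery: a small loss of precision and interpretability, not bias

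*Protocol article*

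**What the plan says.** Under Eligibility criteria, women aged 18 or over qualify "with a diagnosis of GDM during any pregnancy resulting in delivery in the last 60 months". Current pregnancy is excluded, but no minimum time since birth is stated. The Protocol version section explains how the window came about: the third amendment moved it "from recruited within 36 months of most recent delivery to recruited within 60 months of any delivery". Because any GDM pregnancy in the window counts, a woman may also have had a later birth without GDM.

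Randomisation is stratified by age (cut at 30 years) and ethnicity. Under Statistical analysis, change in total activity is regressed on arm, with "terms for the stratification factors as confounders, and adjustment for the change in accelerometer wear time and baseline total physical activity". The same section states: "Interaction effects will be fitted between intervention arm and age (< median vs ≥ median), and ethnicity (White European vs other". Secondary outcomes follow similar methods. Time since delivery is not a stratification factor, a covariate or an interaction.

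The Discussion paragraph of the abstract says that the programme, if effective, "could be translated into a primary care-based intervention that women with GDM are referred to in the postnatal period".

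**The concern.** The outcome is change over the 12 months after baseline. For a woman enrolled a few weeks after birth, those months are her baby's first year. For a woman enrolled four years after birth they are not. It is plausible that the two would follow different courses in activity, weight, waist and sleep with no programme at all.

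Baseline activity in the model absorbs the part of this that is already visible at entry. It cannot absorb the part that lies ahead, since two women with the same low baseline value may be on different natural courses.

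Two things are at stake. The first is precision: a predictable source of variation, fixed before randomisation, is left in the error term. The second is interpretation: the article itself lists barriers to lifestyle change in women with recent GDM, such as lack of time and of childcare, so uptake and effect could differ with time since birth. Nothing planned would show this.

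**Working it through.** **Inputs from the Sample size and Statistical analysis sections.** Target difference 2.1 mg (milligravity), SD 5.3 mg, 80% power, two-sided 5%, 1:1 allocation, 202 evaluable (101 per arm), 290 recruited. Interactions are tested at the 10% level.

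**Assumptions, because the documents give no figure.** R², the share of residual variance that time since delivery explains beyond the terms already in the model: 0 to 0.20. p, the share of women in an early postnatal group: 10% to 50%.

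**1. The plan's own figure.** n per arm = 2 × (1.960 + 0.842)² × (5.3/2.1)² = 100, so 200 in total by the normal approximation. The t-test version gives 100.96, hence 101 per arm and 202 in total, as stated. Then 202/(1 − 0.30) = 288.6, so 289, which becomes 290 in equal arms. The stated sample size reproduces with no visible credit for covariates.

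**2. Gain from adding the covariate.** The standard error of the treatment effect is 5.3 × √(2/101) = 0.746 mg, and power is Φ(2.1/0.746 − 1.96) = 80.4%. With the covariate the residual SD becomes 5.3 × √(1 − R²):

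- R² = 0.01: SD 5.273, power 80.8%
- R² = 0.05: SD 5.166, power 82.4%
- R² = 0.10: SD 5.028, power 84.3%
- R² = 0.20: SD 4.740, power 88.3%

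**3. What such an R² would require.** If a share p of women is early postnatal and their natural 12-month change differs from the rest by d after baseline adjustment, then R² = p(1 − p)d²/5.3². With p = 0.30, R² = 0.01 needs d = √(0.01 × 28.09/0.21) = 1.2 mg, and R² = 0.10 needs d = √(0.10 × 28.09/0.21) = 3.7 mg. A natural difference as large as the target effect (d = 2.1) gives R² = 0.21 × 4.41/28.09 = 0.033 and power of about 81.7%. Values of 0.10 and above are therefore generous.

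**4. Cost if the covariate is useless.** The planned model has six coefficients (intercept, arm, two strata, wear-time change, baseline), leaving 202 − 6 = 196 residual degrees of freedom. One more term leaves 195.

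**5. What an interaction could show.** For an early-versus-late split, SE = 5.3 × √(4/(202p) + 4/(202(1 − p))). At the 10% level:

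- p = 0.10: SE 2.486 mg, power 21% for a 2.1 mg difference in effect; detectable with 80% power: 6.18 mg
- p = 0.20: SE 1.865 mg, power 30%; detectable 4.64 mg
- p = 0.30: SE 1.627 mg, power 36%; detectable 4.05 mg
- p = 0.50: SE 1.492 mg, power 41%; detectable 3.71 mg

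The split only shows the scale; the proposed variable is continuous.

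**The case against.** The strongest reply is that the article sets out a coherent model and that one more prognostic covariate is a preference, which the unseen full protocol or analysis plan may already include. Part of this stands: nothing is misstated, and if the analysis plan adds the term, the point is met. But the article does not leave the model open. It names the covariates and the interactions, so the comment concerns what it fixes.

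Four stronger readings are tempting, and the documents do not support them.

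- *The intended postnatal use goes untested.* This takes postnatal in the abstract to mean the months just after birth. The Background section on maternal outcomes counts the first five years as the postnatal window for intervening, which equals the 60-month entry window. On the article's own terms the trial enrols the intended population. What is not described is whether the effect is similar early and late within that window. The main Discussion section speaks of delivery to high-risk women in various settings and makes no separate claim about postnatal referral.
- *Chance imbalance in early-postnatal women is a further distortion.* With p = 0.30 and d of 2 to 4 mg, the imbalance has an SD of √(2 × 0.21/101) × d = 0.13 to 0.26 mg. Against the standard error of 0.746 mg that is 3% to 12% of the variance, exactly the share given by p(1 − p)d²/5.3². It is the same quantity seen from another side, and it is already inside the confidence interval. Randomisation rules out systematic bias.
- *The trial is underpowered as a result.* The 202 takes no visible credit for covariates, so leaving one out does not weaken it.
- *The conclusion should be limited to the times since delivery where the effect is shown.* With 30% early women (about 61 of 202), the 95% interval for their effect is ± 1.96 × 5.3 × √(4/60.6) = ± 2.7 mg. Power to show a true 2.1 mg effect in them alone is about 34%, so such a rule would usually discard a true conclusion.

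**Conclusion.** The point holds as a modest improvement. The window from soon after birth to 60 months has no lower limit, and time since delivery is absent from the stratification, the model and the interactions. The consequence is some avoidable residual variance and no description of how the effect varies across the window. It is not bias and not an error in the sample size.

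For an assumed R² of 0.01 to 0.10 the gain is about 0.4 to 4 percentage points of power; at R² of 0 there is none. The size rests entirely on that assumption. An interaction analysis at this sample size would give an estimate with a wide interval, not a firm test.

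**What to change.** In the Statistical analysis section:

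1. Add time since delivery at baseline as a prespecified continuous covariate in the primary and secondary models, with its functional form fixed in advance. Time since the most recent delivery is the more relevant variable. Eligibility guarantees only the date of the GDM delivery, and the Demographics and medical history section lists number of children but no date of last birth. Use the most recent delivery if its date is recorded, and otherwise the GDM delivery.
2. Report an exploratory arm-by-time-since-delivery estimate with a confidence interval, labelled as low-powered (about 21% to 41% for a 2.1 mg difference at the 10% level). Do not make the main conclusion depend on it.

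In the Discussion paragraph of the abstract, state that the postnatal period means up to 60 months after delivery, as studied.

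The cost is about one degree of freedom, one extra exploratory estimate and a clause of text. Obtaining the date of the most recent birth may need one extra question or a record check. Recruitment, visits and sample size do not change.
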